### Recruitment

Participants will be recruited via a Google AdWords campaign. Depending on the words a person enters into the Google search engine, certain pages are suggested to them and most people look at the top results of the Google search. Here it is possible to place an advertisement for a fee per click, which is then displayed directly at the top. In our study, such an advertisement will direct the user to a website with information about the study and a further link to the online baseline assessment. The advertisement for Restart is displayed by entering relevant keywords such as “problematic + gambling + help”. The Google AdWords campaign will be launched in Germany, (German-speaking part of) Switzerland and Austria.

### Eligibility criteria

The participants have to fulfill the following criteria to be included in the study:Age between 18 and 75 yearsAgreement to participate via electronic informed consentInternet accessSufficient command of the German languageWillingness to participate in two online surveysWillingness to participate in the self-help training over a period of 8 weeksWillingness to provide an (anonymous) e-mail address (we provide information about how to set up an anonymous e-mail address without including their real name)Presence of psychological strain, subjective feelings about having a problem with gambling and desire for treatment (participants with a South Oaks Gambling Screen (SOGS) sum score < 1 will be excluded from the analyses)

Individuals are not included in the study if they have a lifetime diagnosis of a schizophrenia spectrum or bipolar disorder or if they are acutely suicidal (assessed by one item on suicidality of the PHQ-9). Suicidal individuals are provided with help facilities and telephone numbers to contact in acute cases.

### Randomization

Participants will be randomly allocated to one of the two conditions (intervention group or wait-list control group). The randomization plan will be created from an independent researcher by using block randomization with four participants per block to assure that group sizes are equal. There is no need for concealment of allocation, as allocation here differs from the standard procedure in which study members actively approach participants and where there is previous contact between the researcher (or person who is performing the allocation) and the participants. In this study, participants click on the Google advertisement and if they are interested in participating they start with the baseline online assessment. After completion of the baseline assessment, the researcher obtains the information by e-mail that a new participant has completed the baseline assessment. He then allocates the participants to the two conditions according to the randomization plan. This is performed chronologically, i.e. based on the time and date of completion of the baseline assessment, to prevent any arbitrary allocation of participants. The person (first author) who is allocating the participants thus has no influence on the randomization and enrollment process.

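### Allocation concealment is waived for an inadequate reason while the first author assigns by hand from fixed blocks of four, so upcoming allocations can be known to the allocator

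*Protocol article*

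**What the plan says.** All of this is in the protocol article.

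- **Waiver (Randomization).** "There is no need for concealment of allocation, as allocation here differs from the standard procedure". The reason offered is that study staff do not approach participants and have had no contact with them beforehand.
- **Who makes the plan (Randomization).** "The randomization plan will be created from an independent researcher". The method is "block randomization with four participants per block to assure that group sizes are equal".
- **Who applies it (Randomization).** The researcher learns by e-mail that a baseline assessment has been completed. "He then allocates the participants to the two conditions according to the randomization plan". The section identifies this person as the first author.
- **Safeguard (Randomization).** Assignment is chronological, "based on the time and date of completion of the baseline assessment, to prevent any arbitrary allocation of participants". From this the section concludes: "The person (first author) who is allocating the participants thus has no influence on the randomization and enrollment process".
- **Entry and screening.** Participants enter by themselves: "participants click on the Google advertisement and if they are interested in participating they start with the baseline online assessment". Under Study design, inclusion and exclusion criteria are screened inside the online baseline survey, before randomization. The article does not say whether that screening is automatic.
- **Size and timing.** Sample size plans 136 participants, 68 per condition. Trial status gives a start on 20 January 2018, with recruitment still running at submission and expected to end in February 2019.

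**The concern.** Concealment means that nobody who can affect whether, or in what order, a person enters the sequence knows the next arm. Previous contact with participants is one route by which foreknowledge does harm, but not the only one. In this trial a human step lies between baseline completion and assignment, and the person who takes it works from the plan.

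The statement that this person has no influence is drawn from the chronological rule. Such a rule protects the sequence only if it is enforced or checked, and neither is described. If a doubtful, incomplete or duplicate entry has to be accepted or set aside by someone who knows the next arm, the groups can differ from the start. Selection of that kind cannot be reliably repaired in the analysis.

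**Working it through.** The plan gives no figure on this point to reproduce, so the check is a consistency check, a count of predictable allocations and a comparison of statements.

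**Inputs.** Block size 4, from Randomization. Total 136 with 68 per condition, from Sample size. Each block therefore holds two assignments to each arm. I assume that the six possible orders within a block are equally likely.

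**Consistency.** 136 / 4 = 34 complete blocks, and 34 × 2 = 68 per arm. The block size fits the planned numbers.

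**Case A: the allocator can read the plan ahead.** Every next assignment is known: 136 of 136, or 100%. This is conditional, because the article does not say whether the plan can be read ahead.

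**Case B: the allocator knows only past assignments and the block size.**

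- First two assignments equal: probability 2/6 = 1/3. The third and fourth are then certain, giving 2 certain assignments.
- First two assignments different: probability 2/3. Only the fourth is certain, giving 1.
- Expected certain assignments per block: 2 × 1/3 + 1 × 2/3 = 4/3. As a share: (4/3) / 4 = 33.3%.
- Over the trial: 34 × 4/3 = 45.3, about 45 of 136.

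The probability of a correct guess, always choosing the arm with more places left and tossing a coin when they are equal, is:

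| Position in block | Probability correct |
|---|---|
| 1 | 1/2 |
| 2 | 2/3 |
| 3 | 1/3 × 1 + 2/3 × 1/2 = 2/3 |
| 4 | 1 |

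The mean is (0.500 + 0.667 + 0.667 + 1.000) / 4 = 2.833 / 4 = 70.8%, against 50% under simple randomization.

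**Can foreknowledge be acted on?** Two things would allow it: discretion over who enters the sequence, or discretion over the order.

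- *Order.* A rule based on completion time is stated. Enforcement or audit is not.
- *Entry.* Screening sits inside the survey, which points away from the allocator. It is not said to be automatic. The article states no rule for incomplete or duplicate entries. Such entries are plausible, since Ethical aspects and data safety describes participation under an anonymous e-mail address and Study design offers a 20 Euro voucher for the second assessment.

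Discretion is therefore neither described nor excluded.

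**The case against.** The strongest defence is that this procedure leaves the allocator little to act on. Participants find the study through an advertisement and complete the survey unaided, and the e-mail arrives only after baseline completion. No name, telephone number or address is requested, and there is no interview. Most eligibility criteria are self-declared, suicidality is read from a questionnaire item, and the gambling-screen cut-off is numeric. The order of assignment is fixed in advance by completion time, which is more than reliance on good will because it can be audited. All of this stands, and it makes the risk smaller than in a trial where staff recruit face to face.

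It also rules out three stronger readings that a reader might infer.

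- *The allocator is the person who enrols.* The article describes self-entry and online screening, and gives the first author only the allocating role.
- *The list is open and every next allocation is known.* The article says that the first author assigns according to the plan. It does not say that the whole plan can be seen ahead, so the 100% figure holds only if it can.
- *Selection bias has occurred.* Nothing in the article shows this.

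The predictability of blocks is also secondary. With the plan in hand, block size makes no difference. Without it, a good guess does harm only if the allocator can act on it.

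The defence does not rescue the waiver. Its facts lower the risk, but they do not show that the next arm is hidden from the person making the assignment, or that every decision before assignment is automatic. Nor can the gap be put down to a detail left to a fuller document, because the article states the waiver as a rule.

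**Conclusion.** The point holds in a limited form. The protocol waives concealment on a ground that does not justify it, has the first author assign by hand from a fixed-block plan, and describes no withholding of the sequence and no enforcement of the chronological rule. Upcoming allocations can therefore be known to the allocator: all of them if the plan can be read ahead, and 33.3% with certainty (about 45 of 136) from past assignments alone.

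Confidence is high for the waiver and the arithmetic. It is lower for the route from foreknowledge to bias, which depends on discretion that the article neither describes nor excludes. The weakness should be corrected. It does not show that the trial is invalid.

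**What to change.** 1. **Remaining participants.** The independent researcher who created the plan keeps it and releases one assignment at a time, on receipt of participant ID and completion timestamp and after eligibility is locked. If the survey or program software can assign automatically at that point, this serves equally well; the article does not say whether it can.
2. **Block size (secondary).** Preferably use randomly varying block sizes, for example 4, 6 and 8, and do not disclose them to the allocator.
3. **Text.** Replace the claim that concealment is not needed with a description of what was actually done: who held the plan, whether it could be read ahead, whether screening was automatic, and how incomplete or duplicate entries were handled.
4. **Participants already randomised.** Check baseline-completion timestamps, and any exclusions made after baseline, against the order of the plan, and report every deviation. A clean result would support the procedure used.

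The cost is a short amendment, a small coordination step for each participant, and slightly less exact balance if block sizes vary. Depending on how far recruitment has advanced, items 1 and 2 may reach few participants. Items 3 and 4 remain feasible after recruitment closes.

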### Intervention

The Internet-based intervention, Restart, consists of 11 modules that are based on CBT principles but also includes elements of its third wave, including mindfulness-based and metacognitive techniques. Comorbid emotional and mood problems are also addressed in the program, as they often accompany gambling problems and are assumed to be involved in the onset and maintenance of problematic and pathological gambling [9, 35]. There are more generic modules, e.g., focusing on sleep hygiene, positive activities, social competence and self-worth, however, all modules address pathological gambling with case examples. Furthermore, there are modules on the regulation of debts, handling gambling impulse, adapting gambling-specific thought distortions and relapse prevention, which are more specific to pathological gambling (see Table 1 for an overview). The modules all have an interactive format with exercises and worksheets. The program is text-based with a number of audio files (e.g., mindfulness-based relaxation and breathing exercises) and videos with psychoeducational content (e.g., about a model of the development of sleep disturbances) to make the intervention more appealing. Participants can freely choose in which order they want to work on the modules. We recommend participants to work on one or two modules per week. The duration of each module varies from 30 to 60 min. The participants have the opportunity to communicate with a personal moderator (optional). The moderator helps in case the participant has questions about the program or problems with exercises. Messages are answered within three workdays. If the participant does not use the program, the moderator reminds the participant to work with the program by sending messages including a program overview to enhance adherence. Furthermore, a smartphone app can be used in combination with the desktop Internet-based intervention. The app provides a total of 50 small exercises that refer to content of Restart but is otherwise independent of the portal. The app sends daily reminders via push messages at freely definable times, so that users remember to take time for their mental health in everyday life.

**Table 1 Tab1:** “Restart” modules

Module Title	Description
Introduction	Introduction to features of the program; demonstration of the interaction between thoughts, emotions and behavior
ABC	Introduction to a psychological method to understand how certain feelings and behaviors arise
Handling of gambling impulse	Detection of triggers and strategies to deal with the urge to gamble
Money	Development of monthly/daily lists of debts, expenses and income; Learn strategies to resist the temptation to spend money thoughtlessly
Positive activities	Gives advises on how to integrate positive activities into daily routine; goal formulation; effective planning of activities and long-term goals
Self-worth	Detection of own strengths and valuing self-perception
Social competence	Demonstration of strategies of expedient, cooperative and firm communication
Mindfulness Sleep hygiene	Presentation of mindfulness-based relaxation and attention exercises (e.g., relaxation and breathing exercises, body scan, yoga elements) Explains the importance of sleep quality and gives advice on improving sleep hygiene.
Modifying thoughts	Gives advises on how to adapt depressive and gambling-specific dysfunctional thoughts (e.g., negative filter, gambler’s fallacy, illusion of control) into more realistic/balanced thoughts; metacognitive elements
Relapse prevention	Identification of warning signals for relapse and find strategies to deal with those

### Measures

The primary outcome measure is the post-assessment reduction in gambling-related symptoms, for example, thoughts on gambling and gambling behavior (as assessed by the PG-YBOCS [36]). Secondary outcomes include the reduction in depressive symptoms and gambling-related dysfunctional thoughts (assessed by the PHQ-9 and GABS).

### Primary measures

#### Pathological Gambling Adaptation of Yale-Brown Obsessive Compulsive Scale (PG-YBOCS)

The PG-YBOCS [36] assesses the severity of gambling symptoms. The questionnaire includes two subscales: urges and thoughts associated with gambling and actual gambling behavior. The sum score of each subscale ranges from 0 to 20. The total score can be interpreted as follows: 0–7 sub-clinical, 8–15 mild, 16–23 moderate, 24–31 severe and 32–40 extreme gambling symptoms. The time frame is the past week.

### Secondary measures

#### Patient Health Questionnaire - 9 depression module (PHQ-9)

The PHQ-9 [37, 38] is a self-rating questionnaire to measure depressive symptom severity. The PHQ-9 has high internal consistency (Cronbach’s α = 0.86–0.89; [38]). Its sum score ranges from 0 to 27, with scores from 0 to 4 indicating minimal depression, 5–9 mild depression, 10–14 moderate depression and 15–27 severe depression. The time frame is the past week.

#### Gambling Attitudes and Beliefs Survey (GABS)

The GABS [39] is a self-report questionnaire that explores gambling-related dysfunctional beliefs, such as illusion of control and superstitious thinking. We will use a 15-item short version of the GABS, with all items that were examined when using item response theory [40]. Internal consistency of the whole scale is reported as good (Cronbach’s α > 0.9) [41]. Responses must be given on a 4-point Likert scale (from “strongly agree” to “strongly disagree”). The questionnaire refers to the current state of assessment time.

#### South Oaks Gambling Screen (SOGS)

The SOGS [42] is a 20-item self-report measure to assess engagement in gambling activities and problems related to gambling. The questionnaire is the most frequently used instrument to measure gambling problems internationally and has moderate internal consistency (Cronbach’s α = 0.69) and good convergent validity, as it is strongly correlated with both the *Diagnostic and Statistical Manual of Mental Disorders* (DSM)-IV and DSM-5 criteria for pathological gambling (*r* = .66) [43]. We use the SOGS as a screening instrument for pathological gambling. Sum scores of 0–2 designate non-problematic gambling, scores of 3–4 designate at-risk gambling and scores of 5–20 designate pathological gambling.

#### Web Screening Questionnaire (WSQ)

The WSQ [44] is a brief online self-report screening instrument that assesses the following common mental disorders: depressive disorders, alcohol abuse/dependence, general anxiety disorder, posttraumatic stress disorder, social phobia, panic disorder, agoraphobia, specific phobia, obsessive compulsive disorder and suicide risk. The screening instrument has values for sensitivity ranging between 0.72 and 1.00 and for specificity between 0.44 and 0.77. Participants will only be screened at baseline.

#### Subjective appraisal of the program

The subjective evaluation of the program is assessed by 15 specially created questions on the quality, utility and applicability of Restart (see Additional file 1) and by the German version [45] of the Client Satisfactory Questionnaire (CSQ-8) [46].

### Statistical analyses

Both the intention-to-treat (ITT) and per-protocol samples will be analyzed using linear mixed-model repeated measures ANCOVA with pre-to-post intervention time as the within-group factor, condition as the between-group factor and baseline scores as the covariate. Baseline differences between the two groups will be assessed using the independent samples *t* test for continuous variables and the chi-square test for categorical variables. Missing values for ITT analyses will be imputed using two different methods: (1) maximum likelihood estimation and (2) multiple imputation. In addition, we will conduct an exploratory moderation analysis to see which factors potentially have a moderating influence on symptomatic improvement using the SPSS macro PROCESS (developed by A. Hayes).

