**Method:**

A randomized controlled trial with two conditions (intervention group and wait-list control group), two assessment times (reassessment after 8 weeks) and a total of 136 participants is planned. The primary outcome will be change in pathological gambling measured with the Pathological Gambling Adaptation of Yale-Brown Obsessive-Compulsive Scale from pre to post intervention. The change in depressive symptoms (assessed with the Patient Health Questionnaire - 9 depression module) and gambling-related dysfunctional thoughts (assessed with the Gambling Attitudes and Beliefs Survey) will represent secondary outcomes. The intervention includes modules on debt management, impulse control, gambling-specific cognitive biases, self-esteem, social competence, sleep hygiene, mindfulness and positive activities.

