## Methods

### Study design

The self-help program is evaluated in the framework of a RCT with parallel assignment to two conditions. The intervention group receives Restart over a period of 8 weeks and will be compared with a wait-list control group, which receives full access to the program following the post-intervention assessment. There are two assessment points (baseline and post intervention), where data are obtained by an Internet survey using Unipark®. At baseline, sociodemographic and psychopathological data are assessed; at the post-intervention assessment, psychopathological data and subjective evaluations of the Internet-based intervention (only for the Restart intervention group) are assessed. Within the online baseline assessment, participants are screened for inclusion and exclusion criteria before randomization. All participants will be invited to participate in the post-intervention assessment 8 weeks after the baseline assessment. As an incentive, the completion of the follow-up assessment will be rewarded with a 20 Euro Amazon voucher and all participants will receive access to another Internet-based training intervention to reduce the problematic gaming behavior (retraining). See Fig. 1 for a schedule of enrollment, interventions and assessments (SPIRIT).

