### Sample size

The sample size was calculated using G*Power [31], which indicated an entire sample size of 90 to detect a medium effect of *d* = 0.5, with α = 0.05 and power of 0.80 for analysis of covariance (ANCOVA). Based on previous studies of adherence in Internet-based interventions [32, 33] and among pathological gamblers [34], we expect a dropout rate of 50%. Taking this into account, the total sample size should be 136 with 68 participants in each condition.

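### The primary model uses the baseline score both as an outcome value and as a covariate: ANCOVA's precision is lost, and at 50% dropout a standard likelihood fit understates the standard error

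*Protocol article*

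**What the plan says.** Study design: "There are two assessment points (baseline and post intervention"), eight weeks apart.

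Statistical analyses: the intention-to-treat and per-protocol samples are both analysed by "linear mixed-model repeated measures ANCOVA with pre-to-post intervention time as the within-group factor, condition as the between-group factor and baseline scores as the covariate". The section does not say which term is the treatment test, states no baseline × time term and names no covariance structure. Missing values in the intention-to-treat analysis are to be "imputed using two different methods: (1) maximum likelihood estimation and (2) multiple imputation".

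Abstract, Method: "The primary outcome will be change in pathological gambling measured with the Pathological Gambling Adaptation of Yale-Brown Obsessive-Compulsive Scale from pre to post intervention".

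Sample size: 90 participants "to detect a medium effect of *d* = 0.5", "with α = 0.05 and power of 0.80 for analysis of covariance (ANCOVA"). For attrition, "we expect a dropout rate of 50" per cent, and the total is set at 136, 68 per arm.

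**The concern.** With two assessments, a two-level time factor needs the baseline score in the outcome vector. The covariate is that same score, so at the pre time point the outcome equals its covariate. One slope must then serve two different relations: 1 at pre and ρ at post (in standardised scores).

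Two things are at stake for the primary efficacy test. First, the trial is sized for ANCOVA, but the stated model does not deliver ANCOVA's precision. Second, every participant contributes an artificially small pre residual, while only about half contribute a post residual. A pooled residual variance is therefore too small for the post comparison, and the test rejects too often.

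**Working it through.** **Inputs.** From the article: two assessments, d = 0.5, α = 0.05, power 0.80, 68 per arm, 50% dropout. Assumed: ρ, shown over 0.3 to 0.7; normal scores with SD 1.

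**1. The plan's own figure.** For two groups, d = 0.5 is f = 0.25. The F test needs 128 in total without variance reduction. With the ANCOVA factor 1 − ρ², N = 90 is reached at ρ ≈ 0.55 (f = 0.30, i.e. d = 0.6, would also give 90). The stated 90 therefore fits an ANCOVA that takes credit for a correlation the article does not report. Half of 136 is 68 completers, which is used below.

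**2. Complete data.** Write the model as Y = μ + τ·time + α·condition + δ·time×condition + β·baseline + participant term + error. Baseline is constant within a participant, so it drops out of the within-participant contrast and δ is the between-arm difference in mean change. A mixed-model fit agreed with this to about 1e-14.

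Variance factors: change score 2(1 − ρ), ANCOVA 1 − ρ², ratio 2/(1 + ρ). This is 2/1.3 = 1.54, 2/1.5 = 1.33 and 2/1.7 = 1.18 at ρ = 0.3, 0.5 and 0.7.

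| ρ | N for 80% power, ANCOVA / change | Power with 68 completers, ANCOVA / change |
|---|---|---|
| 0.4 | 108 / 153 | 0.60 / 0.46 |
| 0.55 | 90 / 115 | 0.68 / 0.57 |
| 0.7 | 67 / 78 | 0.81 / 0.75 |

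**3. Standard error at 50% random dropout.** With 68 pre and 34 post values per arm, the pooled slope is B = (2·1 + 1·ρ)/3. Because ρ < B < 1, the pre and post residuals have covariance (1 − B)(ρ − B) < 0. A random intercept cannot represent this, so its variance goes to zero. At ρ = 0.5:

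- B = 2.5/3 = 0.833.
- Pre residual variance: (1 − 0.833)² = 0.028.
- Post residual variance: 0.75 + (0.833 − 0.5)² = 0.861.
- Pooled variance: (2 × 0.028 + 0.861)/3 = 0.306.
- Model SE: √[0.306 × (2/68 + 2/34)] = 0.164.
- True variance: 0.75 × 2/34 + 0.333² × 2/34 + 0.167² × 2/68 + 2 × 0.333 × 0.167 × 2/68 = 0.0547, so the SD is 0.234.
- Ratio 0.234/0.164 = 1.43. The nominal 1.96 acts as 1.96/1.43 = 1.37, a two-sided error of about 0.17.

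Simulated type I error (68 per arm, no effect, 50% random dropout, 1,500 runs per setting):

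| ρ | Random intercept | Compound symmetry, negative correlation allowed | ANCOVA |
|---|---|---|---|
| 0.3 | 0.175 | 0.157 | 0.046 |
| 0.5 | 0.157 | 0.151 | 0.045 |
| 0.7 | 0.169 | 0.163 | 0.050 |

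A separate run at ρ = 0.545 gave 0.18 for the random-intercept form. With complete data that form gives 0.075, about 0.07 and 0.06 at ρ = 0.3, 0.5 and 0.7.

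**4. Bias of the likelihood estimate** (ρ = 0.545, true effect −0.50, 50% dropout).

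| Dropout | Stated model | ANCOVA |
|---|---|---|
| Completely random | −0.505 | −0.506 |
| Depends on baseline, equally in both arms | −0.498 | −0.500 |
| Depends on baseline in one arm only | −0.371 | −0.500 |

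The one-arm case follows from the slope error. Logistic dropout with slope 1 per SD shifts the completers' mean baseline in that arm by 0.413 SD, and the bias is about (B − ρ) × 0.413. At ρ = 0.5 this is 0.333 × 0.413 = 0.14. Simulation gave about 0.20, 0.14 and 0.09 at ρ = 0.3, 0.5 and 0.7.

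**The case against.** **This is a condensed article, and the covariance structure may be fixed elsewhere.** That is fair, and the type I figures do depend on it. With complete data, compound symmetry that allows negative correlation holds its level (0.051, 0.051 and 0.055 at ρ = 0.3, 0.5 and 0.7). At the article's own 50% dropout it does not. An unstructured covariance gives no escape: with slope 1 every pre residual is exactly zero and the likelihood is unbounded. The double use of baseline is in the stated model form, not in a detail left open.

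**A baseline × time term would restore ANCOVA.** It restores the estimate exactly. It does not restore the standard error under a random intercept with one residual variance: type I error at 50% dropout was 0.171, 0.168 and 0.190 at ρ = 0.3, 0.5 and 0.7.

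**Perhaps change was meant as the outcome, with baseline as covariate.** The primary outcome wording and the ANCOVA label support this. That analysis gives the same treatment estimate and standard error as ANCOVA of the post score, so nothing would be lost. But it has no within-group time factor, so the sentence would still need correcting.

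**Multiple imputation is also planned.** Imputing from arm and baseline, then comparing change scores, removed the bias (−0.506 in the one-arm case) and held the type I error (0.053 to 0.054). The imprecision remains: SD 0.235 against 0.217 for ANCOVA. Maximum likelihood is the other listed method and stays affected.

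**A stronger reading is tempting.** A reader might infer that any dropout related to baseline biases the result. The documents do not support that: equal dependence in both arms gave no bias, and the article does not predict a difference between arms. Such a difference is plausible when one arm works through a program and the other waits, but that is a supposition. Nor is a change-score comparison on complete data invalid; it is unbiased and only less efficient.

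**Conclusion.** The point holds in this form and should be corrected before analysis. As written, the primary model contains baseline twice. On complete data its interaction is a change-score test with 1.18 to 1.54 times ANCOVA's variance (ρ 0.7 to 0.3), although the trial is sized for ANCOVA. This rests on the covariate entering as a main effect only, which is what the text states, and on time × condition being the treatment test, which it does not say.

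The more serious consequence is a false-positive rate of about three times nominal at the expected 50% dropout, with no assumption about why people drop out. It applies to likelihood fits with a random intercept or compound symmetry. Bias is a conditional, secondary risk: it needs a baseline-dropout relation that differs between arms, and it affects the likelihood analysis but not imputation from arm and baseline.

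**What to change.** Rewrite the model sentence so that baseline is used once. Either of these will do:

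- ANCOVA with the week-8 PG-YBOCS total (or the change) as outcome, condition as factor and baseline PG-YBOCS as covariate.
- A constrained longitudinal model with pre and post as outcomes, a baseline mean common to both arms, time and condition × time, unstructured covariance and no baseline covariate. This can also serve as the planned maximum-likelihood analysis.

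Name the between-arm contrast at week 8 as the primary test, and use the same model for PHQ-9 and GABS. Merely adding a baseline × time term to the present model is not enough, because the standard error stays wrong under a common residual variance.

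Cost: one or two sentences, which can go into the separate amendment foreseen under Trial status. No new data and no change to trial conduct are needed.
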